### Sample size calculation

Earlier tVNS studies with a design similar to AddVNS, which have focused on clinical outcomes rather than biological ones, have shown low to moderate effect sizes^18,19,23,35^. Moreover, depression is a complex and multifactorial disease, which emerges through the long-time interaction between genetic predisposition and environmental factors^78^. Since no prior multi-omics studies on tVNS effects are available, the sample size calculation was based on the average effect sizes reported in existing clinical tVNS studies. This approach assumes that clinical efficacy reflects the aggregate downstream effects of multiple interacting biological pathways underlying tVNS and can therefore serve as a pragmatic proxy of expected average effect size of omics domains in the absence of direct multi-omics effect size estimates. Such an approach can be considered contemporary and appropriate for early-phase or exploratory multi-omics trials^52,79,80^. In addition, the AddVNS study incorporates an internal pilot phase. Should pilot data unexpectedly indicate that the main assumption regarding effect size is significantly inaccurate, sample size estimates will be updated prior to completion of recruitment, in line with established methodological recommendations^81,82^. Using a G-power calculation tool^83^, we estimated a sample size of *n* = 86 (ANOVA with repeated measures, 2 groups, effect size Cohen’s f = 0.25, significance level a = 0.05, power = 0.95, allocation in study arms 1:1, correlation between repeated measures = 0.3).

Based on prior experience with stimulation studies conducted at our clinic^52^, the AddVNS study anticipates a study discontinuation rate (including loss to follow-up) of approximately 30%. To account for this, we plan to recruit up to *n* = 112 participants, ensuring that at least *n* = 86 complete datasets are available for statistically meaningful analyses in accordance with the sample size calculation. Data from participants who discontinue the study will be included in the final analyses under an intention-to-treat framework. In addition, if more than 10% of data are missing, missing values will be handled using established imputation methods and the results will be compared with those obtained from the intention-to-treat analyses. Using heart rate variability-based stratification, among other psychophysiological and fMRI measured (e.g., pupil size), subgroup analyses will be performed.

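### At the protocol's own 30% discontinuation rate, 112 recruits give about 78 complete datasets, not the 86 said to be ensured; the effect on power is modest

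*Protocol article*

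**What the plan says.** All the figures are in the protocol article, section *Sample size calculation*.

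- The G*Power estimate is 86 participants for a repeated-measures ANOVA with two groups, power 0.95, "f = 0.25, significance level a = 0.05", "allocation in study arms 1:1" and "correlation between repeated measures = 0.3". Neither the particular F test nor the number of measurements is given.
- From experience at the same clinic, the study "anticipates a study discontinuation rate (including loss to follow-up) of approximately 30" per cent.
- The response to that rate is: "To account for this, we plan to recruit up to *n* = 112 participants". The sentence continues with the promised result, "ensuring that at least *n* = 86 complete datasets are available for statistically meaningful analyses".
- The same section says that participants who discontinue will be analysed under intention to treat, and that imputation will be used if more than 10% of data are missing.
- It also allows the sample size to be updated after the internal pilot, but only if the effect-size assumption proves to be clearly wrong.

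**The concern.** A recruitment target that allows for dropout is found by dividing the required number of completers by the fraction expected to stay. Here the target appears to have been found by adding 30% to the required number, which gives too few recruits. The protocol ties its power statement to 86 complete datasets, so a reader will take that number as secured when, at the stated dropout rate, it is not. Because 112 is worded as an upper limit, the plan as written leaves no room to make up a shortfall by recruiting further.

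**Working it through.** **Inputs** (all from *Sample size calculation*): required complete datasets 86; discontinuation d = 0.30; planned recruits 112; f = 0.25; α = 0.05; correlation 0.3; two equal groups.

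**1. Reproducing 112**

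- Required number × (1 + d): 86 × 1.30 = 111.8, rounded up to **112**. This matches the printed figure.
- Required number / (1 − d): 86 / 0.70 = 122.9, rounded up to **123** (124 for an even split). This does not match.

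The protocol prints no formula, so the multiplier of 1.30 is inferred from the match. The steps below do not depend on it.

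**2. Complete datasets from 112 recruits**

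- Expected at 30%: 112 × 0.70 = **78.4**. The shortfall is 86 − 78.4 = 7.6, or about 9% of 86.
- Highest rate at which 112 still gives 86: 1 − 86/112 = **23.2%**.
- Chance of at least 86 completers, each recruit independently completing with probability 0.70: P(Bin(112, 0.70) ≥ 86) = **0.069**.

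| Discontinuation | Expected complete from 112 | Chance of at least 86 |
|---|---|---|
| 25% | 84.0 | 38% |
| 28% | 80.6 | 15% |
| 30% | 78.4 | 7% |

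At 35% the expected number falls to 72.8.

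**3. Effect on power**

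The protocol names neither the F test nor the number of measurements m, so both common choices were computed with the noncentral F distribution, with N participants and correlation ρ:

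- Between-factors test: λ = f²·N·m / (1 + (m − 1)ρ), with 1 and N − 2 degrees of freedom.
- Group-by-time interaction: λ = f²·N·m / (1 − ρ), with m − 1 and (N − 2)(m − 1) degrees of freedom.

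An example for the between-factors test with m = 7 and N = 86: λ = 0.0625 × 86 × 7 / (1 + 6 × 0.3) = 37.625 / 2.8 = 13.44, power 0.952. At N = 78, λ = 34.125 / 2.8 = 12.19, power 0.931.

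| Test | m | Power at 86 | Power at 78 |
|---|---|---|---|
| Between-factors | 7 | 95.2% | 93.1% |
| Between-factors | 3 | 88.1% | 84.7% |
| Between-factors | 2 | 81.1% | 77.2% |
| Interaction | 3 | 99.3% | 98.7% |
| Interaction | 2 | 97.2% | 95.8% |

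Of the variants tried (m from 2 to 9), only the between-factors test with m = 7 needs exactly 86 for 95% power. The value m = 7 is an assumption. Two and three measurements are shown because MRI is acquired twice (*MRI scans*) and psychophysiology three times (*Psychophysiological assessment and actigraphy*).

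**The case against.** Four points can be made for the protocol.

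- **The rate is only approximate.** This does not close the gap. A rate of about 23% is needed, and even at 25% the expected number is 84.
- **Discontinued participants are still analysed.** This stands as far as power is concerned: someone who leaves after week 3 contributes baseline and week-3 psychophysiology, and imputation is planned. But partial or imputed records are not complete datasets, which is what the sentence promises.
- **Some of the 30% may be lost late.** The rate includes loss to follow-up, and the follow-up at 6 and 12 weeks after treatment is optional and by questionnaire only (*Study design*, *Follow-up*), whereas the neuroimaging and psychophysiology of the main objective end at week 6. If part of the loss falls after that, more than 78 would have complete main readouts. The split is not given and *complete* is not defined, so this remains possible but cannot be relied on.
- **The pilot can correct the sample size.** The update is tied to the effect size, not to dropout.

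In the other direction, a reader might infer that the shortfall leaves the trial underpowered, at 77% or 85% for readouts taken twice or three times. The documents do not support this. Those values arise only on the between-factors test, where power at the full 86 is already 81% and 88%. Most of the distance from 95% therefore has nothing to do with dropout. The section *Main hypotheses and statistical analyses* puts the focus on longitudinal changes between the arms, which fits the interaction test better, and there 78 still gives more than 95%.

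**Conclusion.** The promise of at least 86 complete datasets is wrong as written. On the protocol's own rate, about 78 are expected from 112, roughly 8 too few, and 86 would be reached about 7 times in 100. This rests only on the three printed figures and, for the 7%, on independent discontinuation at exactly 30%. It does not depend on how 86 was derived or on whether the multiplier was 1.30.

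The consequence for power is modest. Going from 86 to 78 costs about 2 points on the variant that reproduces 86, about 3 to 4 points on the between-factors test with three or two measurements, and leaves the interaction test above 95%. Analysis by intention to treat reduces the cost further. In an exploratory single-centre study this is a wrong figure that should be corrected, not a reason to doubt the design.

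**What to change.** Replace the guarantee in *Sample size calculation* with one of two statements:

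- About 78 complete datasets are expected from 112 recruits at 30% discontinuation, with power restated at 78 for a named F test and a stated number of measurements; or
- 86 complete datasets from 112 recruits requires discontinuation of no more than about 23%, with a reason for expecting that rate in place of 30%.

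Either version should say what counts as a complete dataset, in particular whether the optional follow-up questionnaires are part of it. If the sponsor wishes to keep both 86 and 30%, the matching recruitment figure is 123, or 124 for equal arms.

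The first two options change a sentence or two and need no extra patients. Their cost is a slightly less favourable stated figure, or the need to defend a lower dropout rate. Only the third adds patients: 11 or 12 more.

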### Main hypotheses and statistical analyses

The focus of the statistical analyses in the AddVNS study is to examine the longitudinal changes between the two study arms (tVNS vs. sham tVNS) at the level of neurobiological readouts. Our aim is to identify parameter patterns that allow direct or indirect conclusions *primarily* about the biological effects of tVNS and *secondarily*, its clinical effects. Age, sex, socioeconomic status, BMI, smoking status, and pharmacological treatment (psychiatric and otherwise) as well as comorbidities will be integrated as covariates. Analyses will be performed regularly (e.g., after the pilot phase) as well as at the study’s end.

At the **neuroimaging level**, given the neuroanatomy of tVNS^16^ several functional readouts will be used for the study of tVNS effects over 6 weeks, contrasted against sham treatment. The general underlying hypothesis is that the 6-week stimulation course produces midterm-lasting functional effects that could underlie parallel or future clinical effects.

(i)Functional reward system response changes that comprise the VTA and nucleus accumbens / ventral striatum, and possibly also the locus coeruleus itself, can be detected by the monetary delay reward task^43^.(ii)Exploratively, comparisons of task-free brainstem fMRI data will be performed after brainstem-focused preprocessing, based on reports on short term effects in downstream targets of vagal afferents including the nucleus of the solitary tract, the substantia nigra, subthalamic nucleus and periaqueductal gray^84–87^. Brainstem intrinsic connectivity changes will be explored by simple-ROI-by-ROI cross correlation analysis, and emerging focal brainstem effects can be followed up by seed-to-brain analyses.(iii)Using the short-IST, we investigate if the central cortical mapping of sympathetic-parasympathetic balance – as monitored by the task/rest switches – change over 6 weeks of treatment. Established parametric modulation techniques will be used here to fuse autonomous signals (e.g., heart rate) with the fMRI time series analysis^51^.(iv)NM-sensitive imaging: Direct quantification of the LC (and other structures with a NM-positive signal such as the VTA and the substantia nigra) will be used for baseline/follow-up comparisons after adequate preprocessing to evaluate potential differences in noradrenergic or dopaminergic trafficking. To date, it is not known if mid-term effects (follow-up measurement days after the last tVNS/sham stimulation) can be captured using this technique.

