### Participants

Only adult patients (≥ 18 years) with current MDD or bipolar disorder with current depression (BD) who are treated at the MPIP’s research hospital (either inpatient or day clinic treatment) and are able and willing to give informed consent can participate in the AddVNS study. Inclusion criteria are: (1) age 18–65 years, legally competent and able to provide informed consent; (2) diagnosis of a depressive episode (MDD or BD) according to ICD-10 or ICD-11; (3) signed informed consent documents for the AddVNS study; (4) signed informed consent and participation in the biobanking project of MPIP (Project No. 338 − 15). Exclusion criteria are: (1) age < 18 years or age > 65 years; (2) pregnancy or planning to get pregnant during the study period, breastfeeding; (3) legal supervision; (4) pervasive developmental disorders and/or intellectual disability; (5) acute substance abuse (e.g., alcohol, prescription or illicit drugs); (6) severe neurological disease; (7) anatomical or technical impossibility of tVNS administration (e.g., microtia, anotia, or history of vagotomy); (8) current treatment with an established neurostimulation method (e.g., ECT, rTMS, VNS); (9) metallic foreign bodies, implanted intracranial devices or cerebral shunts; (10) severe general illness (e.g., relevant anemia requiring transfusion, high-grade cardiac arrhythmia, severe cardiomyopathy); (11) active implants (e.g., cochlear implant, pacemaker, implantable cardioverter-defibrillator).

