### Intervention

Participants receive either tVNS or sham tVNS for a period of 6 weeks. Both interventions are administered as an adjunct to TAU, which is provided by the participants’ attending physicians and psychologists according to clinical expertise and guidelines. Both tVNS and sham tVNS intervention are carried out three times a day (morning, noon, evening) from Monday to Friday. Each of the three daily stimulation sessions lasts 30 to 60 min, depending on the individual tolerance (= individual subjective comfort and tolerability of stimulation) of the participant. Flexibility in stimulation duration was permitted to optimize adherence by accommodating individual tolerability, preferences, perceived autonomy, and comfort.

The stimulation is performed with the device tVNS E ^®^ (tVNS Technologies GmbH, Erlangen, Germany). The device is CE certificated and approved as Class IIa medical device under the Medical Device Regulation of the European Union. The device consists of a stimulator the size of a small cell phone and an ear electrode that is placed at the stimulation site.

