## Discussion

In summary, the AddVNS study will investigate the change of multimodal biological markers during adjuvant tVNS and the relationship to clinical course and change in depressive symptoms during adjuvant tVNS in patients with MDD. This will be achieved by leveraging the sham-controlled design.

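### The covariate list leaves out the outcome's baseline value and does not restrict medication and other changeable covariates to baseline

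*Protocol article*

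**What the plan says.** The section on main hypotheses and statistical analyses sets the aim of the comparison: to "examine the longitudinal changes between the two study arms (tVNS vs. sham tVNS"). It then commits to the adjustment set: "Age, sex, socioeconomic status, BMI, smoking status, and pharmacological treatment (psychiatric and otherwise) as well as comorbidities will be integrated as covariates". Neither the outcome's baseline value nor the diagnosis that qualified the patient for entry is on the list, and no covariate carries a time point.

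The Intervention section describes the background treatment: "Both interventions are administered as an adjunct to TAU, which is provided by the participants’ attending physicians and psychologists according to clinical expertise and guidelines". The Measures section takes both past and current medication from patient records, without a date. MRI is acquired twice, at baseline and after the 6 weeks (MRI scans). Psychophysiology is measured three times, at baseline and at weeks 3 and 6.

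The sample size section names "ANOVA with repeated measures, 2 groups, effect size" Cohen's "f = 0.25, significance level a = 0.05", power 0.95 and "correlation between repeated measures = 0.3", giving 86 participants.

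On population, the Participants section admits adults "with current MDD or bipolar disorder with current depression (BD"), while the opening of the Discussion speaks of "change in depressive symptoms during adjuvant tVNS in patients with MDD".

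**The concern.** Two separate matters are at stake.

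- **Precision.** Every main readout has a baseline measurement. If baseline enters only as the first term of a change, and the correlation between visits is low, the subtraction adds more noise than it removes. Using the same baseline value as a covariate avoids this.
- **Bias.** Medication recorded after randomisation can be a consequence of the arm. The article gives reasons why it might be: active stimulation is titrated to a perceptible sensation while sham delivers no current, treating clinicians are not named among those blinded, and the primary hypothesis expects an antidepressant effect. Conditioning on such a variable can shift the arm contrast in either direction. The same applies, less acutely, to comorbidities, BMI and smoking if they are recorded on study.

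**Working it through.** **Inputs from the article.** Correlation ρ = 0.3, f = 0.25, α = 0.05, power 0.95, N = 86, allocation 1:1 (Sample size calculation); two MRI sessions (MRI scans).

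**1. The plan's own figure.** In the usual G*Power form, the between-groups test with m measurements has noncentrality λ = f²·N·m / [1 + (m − 1)ρ]. With m = 7: 0.0625 × 86 × 7 / 2.8 = 13.44, power 0.952. So 86 is reproduced exactly with m = 7 (m = 8 gives 84), a number that the article does not state. The group-by-time test has λ = f²·N·m / (1 − ρ) and needs N = 76 for m = 2 and N = 60 for m = 3. The sizing sentence therefore does not show which test will be used for the readouts.

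**2. Variance for a two-visit readout**, per participant in units of SD², with equal variances at both visits:

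- change score: 2(1 − ρ) = 2 × 0.7 = 1.40
- follow-up value alone: 1.00
- follow-up value adjusted for baseline: 1 − ρ² = 1 − 0.09 = 0.91

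The ratio of adjusted to change is 0.91 / 1.40 = 0.65, equivalent to 1 / 0.65 = 1.54 times as many participants. Over a range of correlations the ratio is (1 + ρ)/2:

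| ρ | change | adjusted | ratio |
|---|---|---|---|
| 0.1 | 1.80 | 0.99 | 0.55 |
| 0.3 | 1.40 | 0.91 | 0.65 |
| 0.5 | 1.00 | 0.75 | 0.75 |
| 0.7 | 0.60 | 0.51 | 0.85 |

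**3. Power at N = 86** (43 per arm). Two-sided t test, noncentrality δ / √(2V/43), where V is the variance from step 2 and δ the assumed week-6 difference in SD:

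| assumed δ | change | adjusted |
|---|---|---|
| 0.4 | 0.341 | 0.485 |
| 0.5 | 0.491 | 0.671 |
| 1.0 | 0.972 | 0.998 |

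The normal approximation gives 0.975 and 0.998 in the last row. These δ are assumptions. Read as a two-visit interaction, f = 0.25 means a difference in change of 4 × 0.25 = 1.0 SD. Read as a between-groups effect, it means 2 × 0.25 = 0.5 SD between arm averages. As a cross-check, the two-visit interaction at N = 86 has λ = 0.0625 × 86 × 2 / 0.7 = 15.36, the square of the change-score noncentrality at 1.0 SD (3.919). The two tests are the same.

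**4. Medication, illustrative only.** All values here are assumed: a true arm effect of 0.50; a medication score with no effect of its own on the outcome; an unmeasured severity factor (variance 1) with loading g = 0.7 on both; residual SDs of 1; and an arm effect *a* on later medication. Adjusting for that medication gives an expected estimate of 0.50 − a·g²/(1 + g²), where g²/(1 + g²) = 0.49/1.49 = 0.33.

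- a = 0: 0.50, no bias
- a = −0.3: 0.60 (simulated 0.61)
- a = −0.5: 0.66 (simulated 0.67)

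Other assumed signs would reverse the direction.

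**The case against.** The strongest reply is that the article names no analysis model. Repeated-measures ANOVA appears only in the sizing sentence, and a statement about longitudinal change between arms is compatible with ANCOVA or a constrained-baseline mixed model. The full research protocol is in a supplement that is not shown, and an analysis plan may settle how baseline enters. This stands in part. A reader might infer that the plan discards baseline, or that its final model is a change-score ANOVA; the article supports neither, because any longitudinal model uses baseline in some form. What remains is that the article does commit to a list, and baseline is not on it.

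The two-visit algebra also applies directly only to readouts such as MRI, not to the three-visit psychophysiology. And at a 1.0 SD difference, power is ample either way.

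On medication, the article is silent about timing rather than wrong. Bias needs two things that it does not assert: that on-study medication is the covariate, and that the arm affects prescribing. A reader might go further and argue that psychotropic drugs act on the pupil, heart rate variability or gut readouts; the article gives no source for that, and the point does not need it.

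The missing diagnosis invites the charge that a strong prognostic factor was dropped. The article gives neither the mix of MDD and bipolar depression nor its prognostic strength, so that charge cannot be sized.

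**Conclusion.** The point holds as a worthwhile clarification of a stated list, not as proof of a wrong analysis. If two-visit readouts are compared as change between arms, the variance at ρ = 0.3 is 1.40 SD² instead of 0.91. The size of the power gain rests on the assumed effect: it is material at 0.4 to 0.5 SD and negligible at 1.0 SD. It would be too strong to say that the trial loses its planned power, since that depends on which reading of f = 0.25 was meant.

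Adjustment for post-randomisation medication is a risk that the wording leaves open; the documents do not show that it will happen. Adding diagnosis is optional. The MDD-only phrase is a minor slip in the Discussion: the Introduction and Study objectives refer to a depressive episode or to depression generally, in line with the entry criteria.

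**What to change.** - Estimate the post-baseline arm differences with the outcome's baseline value as a covariate, or with a longitudinal mixed model that constrains the arms to a common baseline mean.
- State that medication, comorbidities, BMI and smoking enter only as baseline values.
- Report on-study medication change by arm descriptively, not as a covariate.
- Optionally add diagnosis (MDD or bipolar depression) to the list.
- Align the population wording in the Discussion with the Participants section.

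The cost is wording in the analysis section or analysis plan. Baseline readouts, diagnosis and medication are already collected; the only practical step is to date the medication extraction to baseline.

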### Study objectives

The primary hypothesis of our study is that tVNS induces biological and psychophysiological changes in patients with depression, and that the magnitude of these changes is associated with the antidepressant effects of tVNS. All collected data will be used to evaluate whether beneficial tVNS effects (in addition to TAU) can be predicted. Results will be presented on conferences and published in peer-reviewed journals and, if appropriate, on the Max-Planck-Institutes website in plain language for relevant groups (e.g., participants, physicians).

The main objective of the study is therefore to identify neuroimaging and psychophysiological changes associated with tVNS. The study’s secondary objective is the exploratory investigation of individual markers or clusters of clinical, psychometric, and biological markers which may relate to the course of tVNS in depressive patients receiving TAU (multiomics). Moreover, these parameters as well as the course of treatment (e.g. effects and side effects) will be correlated with the tVNS stimulation paradigm, such as current intensity and daily stimulation duration. The collected data will be used to develop predictive models aiming to identify factors associated with beneficial effects of tVNS in patients with depression.

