The stimulation protocol was developed considering earlier tVNS studies and the mandatory sections of the device’s instruction manual^20,21,35^. The stimulation site is the cymba concha of the left ear, since the latter is thought to be exclusively innervated by the vagus nerve^36^. Thus, the left vagus nerve is stimulated (similar to invasive VNS), which is thought to reduce the risk of bradycardia since the right vagus primarily innervates the sinoatrial node of the heart, although human studies are still needed to confirm this distinction and its clinical relevance^37^. Nonetheless, right-sided or even bilateral tVNS has been shown to be safe^15^. Prior to the actual stimulation, stimulation intensity (electrical current) is determined by titration. Here, the highest level (mA) tolerated by the patient, that is the value between the individual perception- and pain threshold, is used for the longitudinal tVNS stimulation. During weekly titration sessions, stimulation intensity was adjusted beginning at the lowest level (0.1 mA) and increased in 0.1 mA increments until a clearly perceptible yet comfortable sensation was achieved, without pain, up to a maximum of 5 mA. Electrical current of the tVNS E ^®^ can be adjusted between 0.1 and 5.0 mA. Other stimulation parameters are set to the device’s default settings: biphasic stimulation, frequency 25 Hz, pulse-pause ratio 28 s : 32 s.

During the first tVNS stimulation session, study personnel provide detailed instructions on how to use the device in person. In the following sessions, participants perform the thrice daily stimulations by themselves and can reach out to study personnel if questions arise. Any adjustments to the current intensity, including titration during the intervention period, are performed by study personnel only. If a participant intentionally alters stimulation parameters including localization of the ear-electrode in a way that endangers either blinding or the study objective, the individual will be excluded from the study. In addition, regular check-ups are performed by study personnel to prevent errors during the stimulation.

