Sham tVNS is performed identical to tVNS, with the only exception that the sham tVNS is conducted with no current using the manufacturer’s tVNS E ^®^ sham electrode. Visually, the sham electrode cannot be distinguished from a regular stimulation electrode. This approach was chosen to maximize discrimination between specific neurostimulatory effects and non-specific contextual or placebo effects, while still matching key elements of intervention.

The time and duration of each stimulation session is documented by the patient. Additionally, the app (*tVNS® Patient*) is used to retrieve, track, and double-check stimulation parameters. This systematic documentation enables dose–response analyses. To prevent unblinding, only investigators responsible for stimulation have access to the app.

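### Session duration and current intensity are not randomised, so correlating outcomes and side effects with them can mistake a tolerance or motivation effect for a tVNS dose effect

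*Protocol article*

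**What the plan says.** Under Study objectives, the article states that the study's parameters and the course of treatment, with effects and side effects given as examples, "will be correlated with the tVNS stimulation paradigm, such as current intensity and daily stimulation duration". Under Intervention, after describing the patient diary and the app record, it adds: "This systematic documentation enables dose–response analyses".

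The same section shows how each exposure arises.

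- **Duration.** "Each of the three daily stimulation sessions lasts 30 to 60 min, depending on the individual tolerance". The reason given is: "Flexibility in stimulation duration was permitted to optimize adherence by accommodating individual tolerability, preferences, perceived autonomy, and comfort". Sessions are "carried out three times a day (morning, noon, evening) from Monday to Friday" for 6 weeks.
- **Current.** The level used is "the highest level (mA) tolerated by the patient, that is the value between the individual perception- and pain threshold". It is re-titrated weekly, and only study personnel may change it.
- **Sham.** Sessions follow the same procedure with a sham electrode and no current. Session time and duration are documented by the patient, with no exception stated for sham.

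Main hypotheses and statistical analyses lists the covariates: age, sex, socioeconomic status, BMI, smoking, medication and comorbidities.

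**The concern.** Randomisation protects the comparison of verum with sham. It does not protect a comparison of participants who received more stimulation with those who received less. Both exposures arise after allocation and depend on the participant's tolerance; duration also depends on preference. Severity, anxiety, motivation and early improvement could plausibly affect how much stimulation a person accepts, and also how mood and autonomic measures change. None of the listed covariates measures sensory threshold, tolerance, motivation, adherence or baseline severity.

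Side effects are the most exposed. Poor tolerability shortens sessions and lowers the current, so side effects can determine the dose. A dose-response reading assumes the opposite direction.

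A dose finding from this trial would carry weight. The Introduction gives limited knowledge of stimulation parameters as one reason tVNS is still regarded as experimental, and the Discussion presents the detailed stimulation record as a strength. The trial could report that longer or stronger stimulation goes with more benefit when people who are doing better simply accept more of it.

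**Working it through.** The plan gives no figure for this analysis, so there is none to reproduce. The check asks how far exposure can vary and how often a null dose effect would look significant.

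**1. Range of exposure (Intervention).** 6 weeks × 5 days × 3 sessions = 90 sessions. At 30 min this is 90 × 0.5 h = 45 h; at 60 min it is 90 × 1 h = 90 h. Total time can differ twofold through tolerance or preference alone.

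**2. False positives in a verum-only correlation.** From Sample size calculation: 86 completers at 1:1, so 43 per arm, and alpha 0.05 (two-sided assumed). Assume no dose effect and one unmeasured trait, correlated rd with duration and ry with outcome. The expected spurious correlation is r = rd × ry. By Fisher's z, the rejection probability is Φ(z − 1.96) + Φ(−z − 1.96), where z = atanh(r) × √(43 − 3).

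| rd, ry (assumed) | r | z | Rejection by formula | Rejection by simulation |
|---|---|---|---|---|
| 0.3, 0.3 | 0.09 | 0.57 | 9% | 9% |
| 0.4, 0.5 | 0.20 | 1.28 | 25% | 25% |
| 0.5, 0.5 | 0.25 | 1.62 | 37% | 37% |
| 0.6, 0.6 | 0.36 | 2.38 | 66% | 67% |

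The simulations used 20,000 replicates.

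**3. What the sham arm can remove.** Sham sessions have a duration but no current. The verum slope of outcome on duration minus the sham slope therefore cancels any selection that works equally in both arms. Three assumptions about selection in sham, over the same four settings and still with no dose effect:

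| Trait–duration link in sham | Rejection, slope difference |
|---|---|
| Same as verum | about 5% in all four |
| Half as strong | 5% to 13% (9% at 0.5, 0.5) |
| Absent | 7%, 15%, 21%, 38% |

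Equal selection is not assured. The article ties duration to tolerability of stimulation. Tolerance of an electrical current can limit duration in verum but not in sham, whereas motivation or preference can act in both. The comparison improves on the verum-only correlation in every setting, but it reaches the nominal level only when selection is equal.

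**4. Current intensity.** Randomization and blinding says weekly titration was done in both groups, but sham delivers no current. A sham setting therefore cannot show how tolerated current relates to outcome, and current has no comparison like the one in step 3.

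**5. Precision.** With equal arms and similar residual and exposure variances, the standard error of a slope difference is about √2 ≈ 1.4 times that of one arm's slope.

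**The case against.** The strongest reply is that the article makes no causal dose claim. The study is exploratory, the sentence follows a secondary objective and speaks of correlation, and the predictive models seek factors associated with benefit. The stated focus is the randomised contrast between arms, which this point leaves untouched. The article also condenses a fuller protocol, and an analysis plan may exist, so the exact estimator may be set elsewhere.

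Much of this stands, and it limits the point in three ways.

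- A reader might infer that participants set their own current by preference. They do not: only study personnel adjust it, and preference is stated for duration alone.
- A reader might infer that the result will be presented as a dose effect. The text supports only that it can be mistaken for one.
- A reader might take the arm-by-duration interaction as a cure. Step 3 of the working shows that it is not.

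The false-positive rates also rest on assumed trait correlations, and the mildest setting gives only 9%.

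The reply does not remove the point. The article itself names the method, correlation, and itself says that the record enables dose–response analysis, without qualification. Integrating the listed covariates would not help, because none of them measures tolerance, threshold, motivation or baseline severity. The objection is to what is stated, not to missing detail.

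**Conclusion.** The point holds in a limited form. Both exposures depend on tolerance, and duration also on preference, so the planned correlation with outcomes and side effects is open to confounding and, for side effects, to reverse direction. Under no dose effect and 43 per arm, a verum-only correlation for duration would be significant in about 9%, 25%, 37% and 67% of trials for the four assumed trait settings. The documents give no values for these correlations, so the rates show scale and are not predictions.

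The sham arm offers a partial check for duration and none for current. The randomised comparison and the primary objective are not affected. The correction is worth making because the claim is stated without qualification and the change is cheap.

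**What to change.** - **Duration.** Replace the correlation with a model of outcome on arm, logged stimulation time and arm × stimulation time, adjusted for baseline outcome. Report the sham slope as a negative control. State that the interaction removes only self-selection common to both arms, because tolerance of the current can limit duration in verum but not in sham. Report it as exploratory, not causal.
- **Current intensity.** Adjust for the first-titration threshold and baseline severity, and label the result descriptive.
- **Side effects.** State that tolerability itself determines the dose, so an association with dose has no clear direction.
- **Intervention wording.** Say that the documentation allows exploratory, observational dose-response analyses, subject to self-selection.

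The cost is analysis wording only, since the article already provides for session times to be recorded. The downside is a wider confidence interval for the interaction, with a standard error roughly 1.4 times that of a single-arm slope, and a more modest claim.
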